#### 16. Information for parents and guardians

An explanation of the nature of the study will be provided to potential participants in *Serer* or *Wolof,* the local languages in Niakhar. An ethno linguist consultant will be used for accurate translation of the information in these dialects.

# 17. Timing

# Actually the preparatory phase will begin in June 2004 at the latest with the informed consent operations. Five months data collections are planed (interventions and malaria morbidity follow-up), starting from September 1st, 2004.

18. Administrative considerations

The IRD Niakhar Project (Unité de Service Niakhar) will be responsible for the administrative aspects of the study . Particular attention will be given to avoidance of any interference with other malaria studies being conducted in Niakhar. After finalisation of the protocol, no changes will be permitted without the agreement of Research Advisory Panel as well as the Niakhar Project. Any change will be formally endorsed, and attached to the original protocol.

The project has already be presented to all the senior staff of the National Malaria Programme.

19. Budget

Details of the budget are given on appendix in the budget template.

19. 1. Personnel

An experienced team is needed for this demanding study. All payments have been worked out in accordance with Senegalese salary scales.

 Assistance of a computer engineer is fundamental. He will help with programming and, supervision of data entry activities. In close collaboration with the main investigator, he will be asked to produce monthly cross tabulations, which summarise the progress of work.

 An assistant field physician, newly graduated from the University of Dakar will help the principal investigator to ensure medical supervision 24 hours a day and 7 days a week throughout the study.

Three qualified nurses will strengthen the medical staff in existing health centres, as the trial will markedly increase the work pressures in these structures. The project activities must be complementary to health centre’s routine activities.

In order to achieve good follow-up of study children 8 field workers and 2 field-supervisors are needed. This number has been carefully determined according to the average number of compounds that a field worker visits in a day.

A qualified, experienced logistician will have under his responsibility all field materials

 At least two drivers are needed to facilitate communication within the team. They will also ensure transportation of staff from village to village as well as between Dakar and the field.

19.2. Equipment

The following items are needed

 Even if cars are for rent at the Institute which accommodate the study, it is more reliable to secure at least one personal car, as by experience we know now that such project depends a lot on logistical means. Actually four cars will be needed by at sometimes.

 Seven reliable motorbikes are also needed for more efficiency of the field workers survey. They will have to visit on average forty children per day, performing required slides when necessary.

 A minor equipment allowance of US$ 2805 is requested for each of the three health centres used for the trial as these structures receive only a little support from the government.

A third microscope is required to help in reading on time all slides collected as an emergency

A new computer is needed to speed up the data entry tasks and to allow other administrative duties inherent to such kind of trial.

Finally, a small generator for the microscopes is essential to supply power cuts which are often in the study area throughout the rainy season.

19.3. Patients costs

All treatment costs and the transport costs needed for study children and their parents to reach a health centre will be reimbursed by the project for its duration. A sum of US$ 7480 is allocated for these reimbursement expenses.

19.4. Travel

Four air tickets for travelling between London and Dakar are requested; these to allow for supervision and exchange of scientists.

19.5. Institutional fees

Overheads are calculated on the basis of 10% of the total budget.

# VII Implications and contributions to the Gates Programme

Our initial study (IPT in Niakhar, Soudano-Sahelian area with seasonal transmission) has shown that this approach to malaria control has the potential to reduce malaria morbidity in children under the age of five-years substantially. However, it is uncertain which drugs regimen would be clinically highly effective whilst exerting the least drug pressure on the parasite. This new study will determine this.

It is ascertained that this project totally responds to the objectives of the Gates programme. The intervening staffs are Senegalese at 100%. Our target is to develop in the mid term a strong and operational team of prominent multi disciplinary local scientists who will then resituate their experience and training for the entire benefit of malaria control by Senegalese and for Senegalese people.

APPENDIX 2: Screening & inclusion questionnaire

# Date: I______I ______I______I

# Identification (Information given by the demographic and epidemiological surveillance & vaccinations card)

- Name
- ID
- Village number
- Household number
- Date of birth
- Mother’s ID
- Mother’s name
- Vaccinations dates

# Informed consent

**YES NO**

## **Inclusion criteria**

- Age between 1 months & 6 years |__| |__|
- Resident during hole malaria season transmission |__| |__|
- Has the parent or guardian given informed consent |__| |__|

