**Sample size:**

- 1680 children aged 1 to 6 years (420 for each of the four arms)

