2.1. Inclusion criteria**.**

Eligible subjects will fulfil all of the following criteria:

Age between 1 to 6 years of age

Informed consent obtained from parents or legal guardians

Permanent resident of the study area without an intention to leave it in the coming six months

No current participation in another malaria study

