The first step will be to hold by June 2004 several community-meeting with all the partners involved in the trial including the villagers. Then, eligible children will be included if they meet the inclusion criteria and if their parents or guardians provide informed consent. The explanation provided to parents will be given in local languages, emphasising the potential public health impact for malaria control of the study (*appendix 1*). When approval is obtained after a medical examination, a study number will be allocated immediately (*appendix 2*). In addition, an ID card will be given to all participants to facilitate identification at every contact, at home or in the health centres. At the time of each drug administration, a clinical examination and an interview of parents will be performed. Children will pass through four teams respectively for identification, clinical examination, blood sampling and anti malarial drug administrations. Those who are febrile at a time of intervention will be tested for malaria and given two days treatment with Coartem® . Haemoglobin levels and drugs resistance markers will be assessed during two cross-sectional surveys conducted at the time of the first drug administration (September 04), and one month after the third and last drug administration (December 04).

1. Randomisation and drug distribution

Individual randomisation is proposed and will be done approximately three weeks before the first sIPT administration planned for early September 2004. Children will be given active drugs according to their allocation group. The investigators who do the randomisation will also separate the regimens into jars, and make a note of the code. They will therefore not be blind, but all field staff and lab staff involved directly in making observation on study subjects or their samples will be blinded to study group.

Individual notice will be given to all participants approximately one week before any intervention. Drugs will be given at the health centres.. For young children, tablets will be crushed, mixed with water and administered. All participants will be under observation for 15 minutes after drugs are taken. In case of vomiting, the drug will be re-administrated.

1. Patient assessment procedures & clinical management

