Parents and legal guardians will also be informed that, on medical grounds, the principal investigator may decide to withdraw the patient. Reason(s) for this withdraw will be noted in the patient record form. In this case as well, study subjects will keep on receiving all the advantages enjoyed by continuing participants.

11. Monitoring

Clinical monitoring will be done as decided by the Consortium. Basically, a Data and Safety Monitoring Board (DSMB) will be set up with the agreement of the London School of Hygiene and Tropical Medicine (LSHTM), the Dakar University (UCAD) and the National Malaria Control Programme (PNLP). Reports of all cases of death will be given to the DSMB.

The DSMB will review the trial protocol and Standard Operating Procedures (SOPs) before the trial commences and decide on the reporting procedure that it requires.

All serious adverse events that occur within seven days of drug administration will be reported to the DSMB.

12. Recruitment and training of staff

Before commencement of the study, three nurses, two field supervisors, two drivers, seven field workers, two-biologist technicians and two data entry clerks will be recruited. A logistician and an IT manager are also needed for the study. Additional staff may be engaged when needed.

A two-day workshop will be held in early August 2004. During this meeting, the principal investigator will explain the aim of the study. Tasks will be allocated with detailed explanations of expectations for each member of the group. A formal assessment of the impact of the workshop on the participant’s understanding of the study procedures will be held. Last but not least, a strong team spirit will be built up during this retreat.

Finally a one-week pilot study will be organised including organisation of drug distribution in the field.

13. Data management

The first step of the data processing will deal with the selection of the approximately 1680 children aged from 1 to 6 years needed for the study (20% future refusal or loss to follow-up taken into account). This will be done using the demographic database of Niakhar.

13.1. Design and organisation of the trial database.

Information will be collected from two sources:

►From the Niakhar demographic database

Identification information of each individual: identification number, surname, first name, date of birth, gender, residency, and identification of parent

►From the sIPT trial

Drug administration: date and place of event

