## **Exclusion criteria**

- Child unable to take or to retain medications |__| |__|
- Existence of respiratory distress |__| |__|
- Existence of serious or chronic illness |__| |__|
- History of drug allergy |__| |__|
- **Is child eligible?** |__| |__|

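### The Appendix 2 screening form sets the lower age limit at 1 month instead of 1 year and has no line for participation in another malaria study

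*Protocol*

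**What the plan says.** Section 2.1 of the protocol lists four inclusion criteria: age, stated as "Age between 1 to 6 years of age"; informed consent; permanent residence; and "No current participation in another malaria study". The study outline gives the same age range under sample size: "1680 children aged 1 to 6 years (420 for each of the four arms". Section 13 (Data management) describes the first step as choosing from the demographic database "approximately 1680 children aged from 1 to 6 years needed for the study".

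Appendix 2 is the form on which a child is screened. Its inclusion list has three items: "Age between 1 months & 6 years", residence through the transmission season, and consent. Four exclusion items follow, and the list ends with the yes/no item "Is child eligible". A block recording antimalarials taken in the past two weeks comes after that item.

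Section 5 (Enrolment procedure and follow-up) says that, once approval is obtained after a medical examination, "a study number will be allocated immediately", and it cites Appendix 2 at that point. Section 18 (Administrative considerations) promises particular attention to "avoidance of any interference with other malaria studies being conducted in Niakhar".

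**The concern.** The form turns the eligibility criteria into a decision about an individual child. Where form and criteria disagree, staff who complete the form correctly can still reach a decision that section 2.1 does not allow. There are two disagreements.

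The first is the age threshold. As printed, the form's age line is satisfied by a child of two months, whom section 2.1 would not admit. The study outline, section 2.1 and section 13 all describe a population from one year upward.

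The second is an omission. The protocol makes non-participation in another malaria study a condition of entry and acknowledges that such studies are under way at the same site. The form gives the screener nowhere to ask or record this. A child enrolled in two malaria studies at once could have malaria incidence or resistance genotypes affected by the other study, and these are the two major endpoints in section V. The protocol does not say what the other studies involve, so this is a possibility that the criterion is there to exclude. It is not a demonstrated effect.

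**Working it through.** No sample size, power or error rate is involved. The check is a line-by-line comparison of section 2.1 with Appendix 2, followed by a check of whether another step in the protocol fills each gap.

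| Inclusion criterion, section 2.1 | Appendix 2 form | Agreement |
|---|---|---|
| Age 1 to 6 years | 1 month to 6 years | No: lower limit differs |
| Informed consent | Consent item present | Yes |
| Permanent resident, not intending to leave within six months | Resident through the transmission season | In substance |
| Not currently in another malaria study | No item | No: criterion missing |

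**Age.** The lower limit is 12 months in section 2.1 and 1 month on the form, so the form admits an extra band of 12 − 1 = 11 months. The study outline and section 13 agree with section 2.1. Nothing elsewhere in the protocol supports a limit of one month.

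**Number of inclusion criteria.** Section 2.1 has four and the form has three, so 4 − 3 = 1 is missing. Some pages were removed from the copy under review, but the criteria list on the form is already closed by the eligibility item. The omission therefore does not look like an effect of that removal.

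**Does another step cover the age line?** Largely, yes. Section 13 selects candidates at 1 to 6 years from a database that holds date of birth, and Appendix 2 carries a date-of-birth field filled from the surveillance records. For an infant to be enrolled, the selection would have to fail or be bypassed, and the date of birth on the page would have to go unnoticed. In that event the age line, as printed, would not stop the enrolment.

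**Does another step cover the other-study criterion?** Not at the level of the child. The items that section 13 takes from the demographic database are identification number, names, date of birth, gender, residency and identification of the parent. Participation in other studies is not among them. Section 18 gives a general commitment by the project and no per-child check.

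**The case against.** The strongest reply is that this is a slip in copying the criteria onto a form. The ungrammatical age line probably stands for 12 months or 1 year. Three other places agree on the intended limit. Section 5 says that children enter if they meet the inclusion criteria, which are those of section 2.1, and nothing says that the form overrides them. All of this stands, and it is why the point is minor. The discrepancy remains, however, because the form is cited where the study number is given and ends in an eligibility decision. A threshold on such a form should be the right one.

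It can also be said that section 2.1 and section 18 together already deal with other studies. They state the rule and the intention. They do not provide a place to record that the rule was checked for each child.

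A reader might infer more than the protocol supports in three respects:

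- **A sizeable number of infants in the trial.** Such a count would treat the form as the only filter and spread ages evenly from one month upward. Section 13 contradicts the first assumption, and the protocol gives no age distribution for the second.
- **Lower incidence in every arm, making the equivalence limit easier to meet.** The limit is 30% against an expected 20% (section 4). The protocol gives no infant incidence for Niakhar. Its background remark that the main burden in seasonal areas lies in older children is general. Any stray infant would also be individually randomised, so no arm would be systematically favoured.
- **Further contradictions among the exclusions.** Respiratory distress appears on the form and is not named in section 2.2, but that section excludes severe conditions by open-ended example, and respiratory distress can be read as one of them. Recent antimalarials are recorded on the form drug by drug, with chloroquine separate, which is what the section 2.2 exclusion needs. Their position after the eligibility item is a matter of layout.

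**Conclusion.** The point holds as an internal inconsistency that is wrong as written and of minor severity. The form's lower age limit contradicts section 2.1, the study outline and section 13. The form also omits one of the four inclusion criteria at a site where the protocol says the matter arises.

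The age error is unlikely to bring infants into the trial, provided that the section 13 selection is carried out as described and the date of birth on the form is looked at. The omitted criterion is the more exposed of the two, because neither safeguard touches it. The size of either effect cannot be calculated from the protocol, and no effect on the incidence comparison or on the equivalence limit is claimed.

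This rests on Appendix 2 being used as its title and the citation in section 5 indicate, that is, as the record of the eligibility decision.

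**What to change.** Before the form is used:

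- Reconcile the age line in Appendix 2 with the age criterion in section 2.1, so that form and criteria carry the same limits.
- Add a yes/no line for current participation in another malaria study to the form's inclusion list.
- Optionally, move the block on recent antimalarials ahead of the eligibility item, so that the section 2.2 exclusion is applied before the decision is recorded.

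The cost is one revision of one form. Sample size, randomisation and analysis are unaffected.

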## **Exclusion criteria**

- Child unable to take or to retain medications |__| |__|
- Existence of respiratory distress |__| |__|
- Existence of serious or chronic illness |__| |__|
- History of drug allergy |__| |__|
- **Is child eligible?** |__| |__|

# Anti malarial treatment received *(within the past two weeks)*

Onset treatment Duration of treatment

- Chloroquine I______I ______I______I I______I ______I______I
- Fansidar I______I ______I______I I______I ______I______I
- Quinine I______I ______I______I I______I ______I______I

- Other I______I ______I______I I______I ______I______I

APPENDIX 4: Passive surveillance / Diohine health centre

Name nurse/clinician and date of consultation:

Name of supervisor and date Supervision:

| **ID** | **Name** | **Mother’s Name** | **DOB** | **Date of reference** | **Date of arrival** | **Temperature** | **Diagnosis** | **Treatment** | **Comment.** |
| --- | --- | --- | --- | --- | --- | --- | --- | --- | --- |
|  |  |  |  |  |  |  |  |  |  |
|  |  |  |  |  |  |  |  |  |  |
|  |  |  |  |  |  |  |  |  |  |
|  |  |  |  |  |  |  |  |  |  |
|  |  |  |  |  |  |  |  |  |  |
|  |  |  |  |  |  |  |  |  |  |
|  |  |  |  |  |  |  |  |  |  |
|  |  |  |  |  |  |  |  |  |  |
|  |  |  |  |  |  |  |  |  |  |

### APPENDIX 5: Adverse Reactions

Village number |___|___| Compound number|___|___|___|

Mother name Mother’s ID Number|___|___|___|___|___|

Child’s name Child’s ID Number: |___|___|___|___|___|

**Notified adverse reactions** **Y** **N**

If yes,

Side effects Date onset Time onset End time Severity[[4]](#footnote-5)1

- |__________| |__________| |___________| |_____|

- |__________| |__________| |___________| |_____|

- |__________| |__________| |___________| |_____|

- |__________| |__________| |___________| |_____|

APPENDIX 6: Microscopy results

Name of the microscopist:

| **ID** | **Nom** | **Date** | Pf asexual | **Pf gametocytes** | **Other P. asexual** | **Other P. gametocytes** | **Comments** |
| --- | --- | --- | --- | --- | --- | --- | --- |
|  |  |  |  |  |  |  |  |
|  |  |  |  |  |  |  |  |
|  |  |  |  |  |  |  |  |
|  |  |  |  |  |  |  |  |
|  |  |  |  |  |  |  |  |
|  |  |  |  |  |  |  |  |
|  |  |  |  |  |  |  |  |
|  |  |  |  |  |  |  |  |
|  |  |  |  |  |  |  |  |
|  |  |  |  |  |  |  |  |

# Appendix 7: Consultation form

Reference form to be collected by the health centre nurse and given to the supervisor

Cher Docteur,

Voudriez vous consulter l’enfant nommé:

ID: Fils/fille de:

Vil/cc: Nom du CC:

Sa température à heures minutes, est de degrés

La famille signale:

Traitement d’attente reçu:

Goute épaisse faite Non faite

Name field-worker:

Signature: Date:

Date de la visite:

Nom de l’infirmier ou du médecin qui a reçu l’enfant :

Notes du superviseur :

**REFERENCES**

1. 1 Every child treated after confirmed malaria will lose 28 days of follow-up

   2 Kaplan Meier Method will be used to plot survival curves, and Logrank test to assess potential differences in the analysis [↑](#footnote-ref-2)
2. 2 [↑](#footnote-ref-3)
3. 1 An Ethno linguist consultant will translate in the information in Serer and Wolof [↑](#footnote-ref-4)
4. 1 Severity: 1=Mild, 2=Moderate, 3=Severe [↑](#footnote-ref-5)
